In phase II, sixteen patients with adenocarcinoma from the digestive system will be enrolled in total. Patients will be treated with the cell dose determined safe in the interim analysis following phase I. They will be divided into two groups: Group 1 consists of patients with advanced disease as defined in phase I and will solely receive MSC_apceth_101 and GCV (Figure 2A). Group 2 comprises of patients with adenocarcinoma that qualify for surgery with prior neoadjuvant treatment. Here, bone marrow shall be drawn prior to the start of the neoadjuvant treatment. Then, during the course of the neoadjuvant treatment, MSC_apceth_101 will be produced. If the patient still qualifies for surgery after re-staging following neoadjuvant therapy, the respective patient will then be enrolled into the trial. MSC_apceth_101 will be administered as a single dose 48–72 hours prior to surgery according to the dose determined in phase I. On day 1–3 following surgery, patients will receive GCV infusions in order to abolish residual MSC_apceth_101 (Figure 3B).

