**Table 1 Tab1:** **Objectives and endpoints of the TREAT-ME1 study**

Objective	Endpoint
Primary	Safety and tolerability of MSC_apceth_101 (phase I and II)
Key secondary	• Total and individual size of relapse/metastases by CT or MRT according to RECIST criteria (phase I/II, group 1)
	• Detection of the therapeutic transgene expressed by homing MSC in resected tumor specimen by PCR technique shortly after its administration (phase II, group 2)
	• For comparison: Detection of the therapeutic transgene expressed by homing MSC in normal tissue adjacent to the tumor (phase II, group 2)
	• Optionally: PET activity in initially PET positive patients (phase I/II, group 1)
	•Tumor/serum markers (phase I/II, both patient groups)
Other secondary	•Time to progression up to 1 year after first MSC_apceth_101 administration (phase I/II)
	• Overall survival up to 1 year after first MSC_apceth_101 administration (phase I/II)

The Safety Set (SAF) of patients, which will be used for analysis of all safety-related data, will include all patients who received at least one dose of MSC_apceth_101. The Full Analysis Set (FAS) will consist of all patients who received at least one dose of MSC_apceth_101 and have at least one disease assessment. Safety-relevant data to determine the primary endpoint of this trial will include reporting of any adverse event, laboratory and other safety parameters determined in the trial visits.

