Footnotes:^1^ not earlier than two weeks after end of chemo-/radiotherapy; ^2^ 24 h (±2 h) inpatient monitoring after end of MSC_apceth_101 infusions;^3^ 24 h (±3 h) inpatient monitoring after start of 1^st^ GCV infusion and including the 3^rd^ GCV infusion (discharge from hospital 2 h after 3^rd^ infusion); ^4^ Before and 15,30,60 min, 2 h, 4 h (±0.5 h), 6 h (±1 h), 8 h (±1 h), 12 h (±3 h), and 24 h (±2 h) after the end of MSC_apceth_101 infusion; ^5^ Before and 15,30,60 min, 2 h, 4 h (±0.5 h), 6 h (±1 h), 8 h (±1 h) after start of 1^st^ GCV infusion and before and 15, 30, 60 min and 2 h after 2^nd^ GCV infusion;^6^ Before and 15, 30, 60 min and 2 h after each GCV infusion; ^7^ Before MSC_apceth_101 infusion; ^8^ Before and 6 h (±1 h) and 24 h (±2 h) after start of infusion of MSC_apceth_101; ^9^ Before and 6 h (±1 h) after start of first infusion of GCV; ^10^ 1.5 h (±0.5 h) after 3^rd^ GCV infusion; ^11^ tumor marker: CEA, CA15-3, CA19-9, CA125, CA72-4, Cyfra21-1, AFP; only tumor marker applying for the tumor entity are determined;^12^ First GCV infusion not earlier than 48 h after preceding MSC_apceth_101 infusion; ^13^ Scans not older than 4 weeks can be used as baseline scans;^14^ MRT or CT or PET whatever was used at visit 1; repeat PET only if PET was done at visit 1; MRT or CT or PET can be carried out up to 28 days after day 56 if this is more convenient for the procedures in the hospital. ^15^ Survival status, any new relapses/metastasis, ECOG, treatment history: chemotherapy, radiotherapy, any other antitumor treatment.

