Footnotes:^1^ in case subsequent chemo- or radiotherapy begins before day 29 all investigations of this day are to be carried out up to 5 days before therapy starts. Thereafter, no further AE recording is required; ^2^ not earlier than 2 weeks after end of chemo-/radiotherapy; ^3^ 24 h (±2 h) inpatient monitoring after end of MSC infusion; ^4^ 24 h (±3 h) inpatient monitoring after start of 1^st^ GCV infusion and including the 3^rd^ GCV infusion; ^5^ Before and 15, 30, 60 min, 2 h, 4 h (±0.5 h), 6 h (±1 h), 8 h (±1 h), 12 h (±3 h), and 24 h (±2 h) after the end of MSC_apceth_101 infusion; ^6^ Before and 15, 30, 60 min, 2 h, 4 h (±0.5 h), 6 h (±1 h), 8 h (±1 h), 12 h after start of 1^st^ GCV infusion and before and 15, 30, 60 min and 2 h after 2^nd^ GCV infusion; ^7^ Before and 15, 30, 60 min, 2 h after the start of each GCV infusion; ^8^ before MSC infusion; ^9^ before 1^st^ GCV infusion; ^10^ Before and 6 h (±1 h) and 24 h (±2 h) after end of MSC infusion; ^11^ Before and 6 h (±1 h) after start of 1^st^ GCV infusion; ^12^ 1.5 h (±0.5 h) after start of 3^rd^ GCV infusion; ^13^ Before and 6 h (±1 h) and 24 h (±2 h) after end of insufion of MSCs; ^14^ tumor marker: CEA, CA15-3, CA19-9, CA125, CA72-4, Cyfra21-1, AFP; only tumor marker applying for the tumor entity are determined; ^15^ Including biopsy of surrounding healthy tissue (will be used to detect MSCs) and should be at least 48 h after MSC infusion.

For the assessment of quality of life, the EORTC QLQ-PAN26 and QLQ-C30 (version 3.0) will be used. The EORTC QLQ-C30 is a questionnaire to measure general quality of life in cancer patients. The questionnaire consists of 9 multi-item scales: five functional scales (physical, role, cognitive, emotional and social), three symptom scales (fatigue, pain and nausea/vomiting) as well as global health and quality of life scales [19]. Specific symptoms including dyspnea, insomnia, anorexia, constipation, diarrhea and financial impact are measured as six single items. The EORTC QLQ-C30 has been used extensively in studies on cancer patients and has proven good internal consistency (alpha > 0.70) and good test-re-test reliability (0.80-0.90) [20].

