### Adverse events (AE)

Registration of any adverse events (AE) following administration of the IMP is a key factor for evaluation of the safety of the IMP. AEs will be defined and evaluated regarding their severity according to the Common Terminology Criteria of Adverse Events (CTC-AE). An AE is defined as the appearance of (or worsening of any pre-existing) undesirable sign(s), symptom(s), or medical condition(s) that occur after a patient received the first dose of IMP and during the following time periods:For phase I and phase II, group 1: from Visit 2 until Visit 15. If any radio- or chemotherapy starts before day 56 the reporting of AEs will be stopped.For phase II, group 2: from Visit 2 until Visit 11 or until start of any radio- or chemotherapy.

It has to be taken into consideration that the safety data evaluation of patient group 2 will be influenced and superimposed by the concomitant surgery and medication and potential other related procedures. The investigator will be asked to evaluate the causal relationship of AE to surgery and/or associated concomitant procedures/medications or to the IMP diligently.

Serious adverse events (SAE) are defined as AEs meeting at least one of the following criteria:Is fatal or life-threateningResults in persistent or significant disability/incapacityConstitutes a congenital anomaly/birth defectIs medically significant, i.e. defined as an event that jeopardizes the patient or may require medical or surgical intervention to prevent one of the outcomes listed aboveRequires inpatient hospitalization or prolongation of existing hospitalization

To ensure patient safety, every SAE regardless of suspected causality, occurring after the patient received the first IMP administration and during the safety time periods as indicated above must be reported in writing within 24 hours of first knowledge of its occurrence. Any SAE arising outside the safety time periods should only be reported if the investigator suspects a causal relationship to the IMP or Ganciclovir.

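### In group 1 the only scheduled post-treatment scan may slip to day 84 and be taken on next-line therapy, and the baseline scan may predate the end of prior therapy

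*Protocol article*

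**What the plan says.** Study rationale names potential benefit by RECIST as an aim alongside tolerability. Table 1 puts the total and per-lesion size of relapses or metastases on CT or MRT first among the key secondary endpoints for group 1.

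Table 2 (group 1) fixes the timing:

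- Screening (Visit 1) is on day −10 to −3. It may be "not earlier than two weeks after end of chemo-/radiotherapy" (footnote 1).
- For the baseline image, "Scans not older than 4 weeks can be used as baseline scans" (footnote 13). The date from which the four weeks run back is not given.
- The one scheduled post-treatment image is at Visit 15, day 56±7. Footnote 14 adds that it "can be carried out up to 28 days after day 56 if this is more convenient for the procedures in the hospital".
- Visits 16–18 have no imaging row. They record "Survival status, any new relapses/metastasis, ECOG, treatment history: chemotherapy, radiotherapy, any other antitumor treatment" (footnote 15).

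The exclusion criteria cover anticipated chemo- or radiotherapy only until two days after the last ganciclovir dose. The adverse-event section provides for therapy that starts earlier than Visit 15: "If any radio- or chemotherapy starts before day 56 the reporting of AEs will be stopped". It says nothing about the scan.

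Group 2 is handled differently. If chemo- or radiotherapy begins before day 29, "all investigations of this day are to be carried out up to 5 days before therapy starts" (Table 3, footnote 1).

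**The concern.** The trial has no control arm, so a change in tumor size can be read as a product effect only if little else happens between the two scans. The schedule leaves three gaps.

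1. The follow-up scan can move by four weeks for a reason unrelated to the patient.
2. New antitumor therapy can start before that scan, and nothing in the article brings the scan forward.
3. Prior chemo- or radiotherapy can still be running when the baseline scan is taken.

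With one scheduled post-treatment scan per patient, a scan taken too late cannot be replaced. The numbers are small: six patients in phase I, and in phase II "sixteen patients with adenocarcinoma from the digestive system will be enrolled in total", divided between two groups. Group 1 therefore has fewer than 6 + 16 = 22 patients, so each contributes more than 1/22 ≈ 4.5% of the tumor-size data.

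**Working it through.** The article gives no power, effect size or sample-size derivation for this endpoint, so there is no planned figure to reproduce. The check is date arithmetic on the schedule, using day numbers as printed. If there is no day 0, intervals that cross it change by one day.

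**Inputs**

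- Visit 1: day −10 to −3 (Table 2)
- Minimum gap from end of prior therapy to Visit 1: 14 days (footnote 1)
- Maximum age of baseline scan: 28 days, reference date not stated (footnote 13)
- Last ganciclovir: day 19 (Table 2)
- Restriction on anticipated therapy ends: 19 + 2 = day 21 (exclusion criteria)
- Follow-up scan: day 49 to 63, or up to 56 + 28 = day 84 (Table 2, footnote 14)

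**1. Possible time on next-line therapy before the scan** = scan day − 21, if therapy starts as soon as the restriction ends.

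- Day 49: 49 − 21 = 28 days
- Day 56: 56 − 21 = 35 days
- Day 84: 84 − 21 = 63 days

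**2. Scan-to-scan interval** = follow-up day − baseline day.

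- Shortest: 49 − (−3) = 52 days.
- Longest, four weeks counted back from day 1: oldest scan on day 1 − 28 = −27, so 84 − (−27) = 111 days.
- Longest, four weeks counted back from Visit 1 on day −10: oldest scan on day −38, so 84 − (−38) = 122 days.
- Ratio of longest to shortest: 111/52 = 2.1 or 122/52 = 2.3.

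**3. Baseline scan before the end of prior therapy** = latest permitted end of therapy − oldest permitted scan. The latest permitted end is Visit 1 − 14.

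| Visit 1 | Latest end of therapy | Oldest scan, from day 1 | Overlap | Oldest scan, from Visit 1 | Overlap |
|---|---|---|---|---|---|
| day −10 | −24 | −27 | 3 days | −38 | 14 days |
| day −3 | −17 | −27 | 10 days | −31 | 14 days |

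An overlap is possible under both readings.

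**4. What the interval alone can do (illustration).** Growth in diameter with no treatment effect is 2^(t/(3·DT)) − 1. DT is the volume doubling time, which is an assumption because the article gives none.

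| Assumed DT | 52 days | 111 days | 122 days |
|---|---|---|---|
| 50 days | 27% | 67% | 76% |
| 100 days | 13% | 29% | 33% |
| 150 days | 8% | 19% | 21% |
| 200 days | 6% | 14% | 15% |

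At any of these rates, permitted scan dates alone more than double the measured change.

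**The case against.** **Direction of bias.** A reader might infer that prior therapy will be credited to the product. The documents do not support that. Group 1 patients must have ended standard therapy and must have progressive disease in the investigator's clinical assessment. In such patients an old baseline scan more likely counts pre-treatment growth against the product. A late follow-up scan without new therapy also leans against it, because the tumor has longer to grow. Only a scan on effective next-line therapy flatters the product. This objection stands: the error can go either way.

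**Response category.** It is also tempting to say that scan timing moves the same tumor from stable disease to progression. That depends on one chosen growth rate and on a category limit that the article does not print. The endpoint is stated as size, and no response-rate analysis is described. The illustration supports added variability and no more.

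**Extremes.** The 52- and 111- or 122-day figures pair the earliest and latest permitted dates at both ends. The 63 days assume therapy from day 21. These are limits of what is allowed, not expected values.

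**The group 2 rule.** Table 3 has no imaging row, so the rule covers tumor markers and tumor status but no scan. It shows that the investigators saw the need to assess before new therapy. It is not a precedent for RECIST imaging.

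**Traceability.** Concomitant medication is recorded through Visit 15 and later antitumor treatment from Visit 16, so affected scans can be identified and an analysis plan can say how to treat them. This is true, but no analysis plan can supply a pre-therapy scan that was never taken.

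**Condensed article.** The full protocol may contain a group 1 scan rule. The convenience delay, the four-week baseline allowance and the two-week gap, however, are explicit rules in the article, not omissions.

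**Conclusion.** The point holds as a weakness in how a key secondary endpoint is timed. As written, the only scheduled post-treatment size measurement in group 1 may be taken as late as day 84 and after up to 63 days of other therapy. Scan-to-scan intervals may differ 2.1- to 2.3-fold between patients. The baseline scan may precede the end of prior therapy by up to 3–10 days (four weeks counted from day 1) or 14 days (counted from Visit 1).

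The date limits follow from the article. The growth percentages rest on assumed doubling times. How often any of this would happen cannot be judged from the documents.

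A reader might conclude that the trial's main result is at risk. It is not: the primary endpoint is safety and tolerability, and the article states no efficacy test whose error rate could change. This is a change that should be made because it is cheap and a missed scan cannot be recovered; the trial does not depend on it.

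**What to change.** Amend Table 2 and its footnotes:

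1. If new antitumor therapy starts before the Visit 15 scan, do the CT/MRT and the tumor markers before its first dose. This concerns when to measure and does not ask for therapy to be delayed.
2. Limit the footnote 14 delay to patients who have not started new therapy, or keep day 56±7.
3. State the date from which the four weeks in footnote 13 are counted, and require the baseline scan to follow the end of prior chemo- or radiotherapy. Footnote 1 already leaves at least 14 days before Visit 1 in which such a scan can be done.
4. Report actual scan dates for every patient. Show any scan taken after new therapy separately, not as product effect. Counting such scans as non-response is not needed, and it would impose a responder analysis on an endpoint stated as size.

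Cost: slightly tighter scheduling and an occasional repeat baseline scan; no scheduled scan is added. A scan brought forward shortens the interval. In the extreme it would be 21 − (−3) = 24 days, which is a further reason to report the dates.

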## Methods/study design

### Study rationale

The highly innovative therapy tested in the TREAT-ME1 study utilizes the patient’s own MSCs to combine cell and gene therapy at a high pharmaceutical quality level. The specific mode of action of the suicide gene engineered into MSC_apceth_101 has the purpose of limiting the toxic gene therapy to the tumor and thus this therapy may display a favorable tolerability and safety profile. Presumably, this yields a high impact for all patients suffering from advanced tumors as the side effects of the standard and second-/third line therapies can significantly hamper completion of full treatment with these drugs. This in turn may provoke development of chemoresistance in tumors. The main rationale for the actively recruiting TREAT-ME1 trial is to demonstrate good tolerability of treatment with MSC_apceth_101 in combination with GCV and to assess a potential therapeutic benefit based on RECIST criteria [16].

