**Table 2 Tab2:** **Investigational schedule for patients in group 1 of phase I and II**

Consultation visit	1	2, 6, 10	3, 7, 11	4, 8, 12	5, 9, 13	14	15	16	17	18
Days	(−10) to (−3)	1/8/15	3/10/17	4/11/18	5/12/19	29±3	56±7	168±14	252±14	336±14
**Parameter**	**Screening** ^**1**^	**MSC_apceth_101 infusion** ^**2**^	**GCV infusions** ^**3**^							
**Informed consent**	X									
**Inclusion/exclusion criteria**	X									
**Medical history/demography**	X									
**Physical examination**							X			
**Adverse events**		X	X	X	X	X	X			
**Concomitant medication**	X	X	X	X	X	X	X			
**Vital signs**	X	X^4^	X^5^	X^6^	X	X	X			
**Body weight**	X	X^7^				X	X			
**12-lead ECG**	X					X	X			
**Cardiac monitoring**		X^8^	X^9^	X^10^						
**Oxygen saturation**		X^8^	X^9^	X^10^		X				
**Tumor markers** ^**11**^	X						X			
**Tumor status**	X						X			
**MSC_apceth infusion**		X								
**GCV infusion**			X^12^	X	X					
**MRT or CT (PET optional)**	X^13^						X^14^			
**QoL assessment**	X					X	X			
**Serum pregnancy test**	X						X			
**Urine analysis**	X						X			
**Hematology**	X	X			X	X	X			
**Blood chemistry**	X	X	X	X	X	X	X			
**Creatinine clearance**	X									
**Inflammation markers**	X					X	X			
**Coagulation markers**	X	X			X	X	X			
**Infectious disease markers**	X						X			
**Lymphocyte subsets**	X					X	X			
**Biomarker samples**		X	X	X^10^						
**Retention samples**		X7				X	X			
**Immunogenicity samples**	X					X				
**ECOG**	X						X			
**Disease status** ^**15**^								X	X	X

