### Safety follow-up

The safety follow-up is not limited to 56 days and 29 days from the IMP administration in group I and II, respectively. Apart from day 56, there are further safety follow-up visits to evaluate the long-term effects. At any time also unscheduled visits are possible.

The safety follow-up visits include visit 16 on day 168 (±14 days), visit 17 on day 252 (±14 days), and visit 18 on day 336 (±14 days). During these visits the disease status, ECOG status, and treatment history for chemotherapy, radiotherapy, surgery, other anti-tumor treatments will be evaluated (see Tables 1 and 2).

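### Group 1: time to progression runs to 1 year, but after the single post-treatment scan (day 49 to 84) nothing scheduled or listed captures growth of known lesions, so the endpoint is likely biased upwards by an unknown amount

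*Protocol article*

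**What the plan says.** Table 1 of the protocol article lists, among the other secondary endpoints, "Time to progression up to 1 year after first MSC_apceth_101 administration (phase I/II". A key secondary endpoint is "Total and individual size of relapse/metastases by CT or MRT according to RECIST criteria (phase I/II, group 1", and the Study rationale section says that the trial aims "to assess a potential therapeutic benefit based on RECIST criteria". The article does not say which events count as progression for the 1-year endpoint.

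Table 2, the group 1 schedule, marks the imaging row and the tumour status row at screening and at visit 15 (day 56±7) only. A footnote widens the scan window: "MRT or CT or PET can be carried out up to 28 days after day 56". At visits 16, 17 and 18 (days 168, 252 and 336, each ±14) the only row marked is disease status, and footnote 15 gives its content: "Survival status, any new relapses/metastasis, ECOG, treatment history: chemotherapy, radiotherapy, any other antitumor treatment".

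The Safety follow-up section describes the same visits: "During these visits the disease status, ECOG status, and treatment history for chemotherapy, radiotherapy, surgery, other anti-tumor treatments will be evaluated". It allows unscheduled visits at any time but attaches no tumour assessment to them.

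**The concern.** Group 1 patients enter with progressive disease, and their relapses or metastases are to be measurable on imaging. Growth of those lesions is an obvious route to progression. Up to the visit 15 scan, both growth and new lesions can be seen. From then until day 336, new lesions are the only tumour finding that the schedule asks for.

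A patient whose known lesions grow after the scan, with no new lesion, could therefore stay in the data as progression-free. The error runs one way, towards a longer time to progression, and in a single-arm trial no control arm shares it. An analysis plan written later cannot recover findings that the visits did not collect.

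**Working it through.** The article gives no event count, median or power figure for this endpoint, so there is no stated figure to reproduce. The check has two parts.

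**1. Schedule arithmetic (Table 2, its footnotes and the Safety follow-up section)**
- Earliest post-treatment scan: 56 − 7 = day 49. Latest: 56 + 28 = day 84.
- Visit 16: day 168 ± 14, so day 154 to 182.
- Shortest interval from scan to visit 16: 154 − 84 = 70 days. Longest: 182 − 49 = 133 days.
- Scans scheduled after day 84: none. Listed items on the size of known lesions after day 84: none.

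**2. Illustration of size (assumptions, not in the documents)**

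Assume exponential time to progression with a true median of 91 days, a growth-only share g of 30% or 50%, and no deaths or dropout. The first infusion is on day 1, so days 56, 84 and 336 are 55, 83 and 335 days from the start. S(t) = 2^(−t/91):
- S(55) = 0.658, S(83) = 0.531, S(335) = 0.078.

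*Upper bound: no patient with growth after the scan later shows a new lesion.* Missed share = g × [S(scan) − S(335)].
- Scan on day 56: 0.658 − 0.078 = 0.580; × 0.3 = 0.174; × 0.5 = 0.290.
- Scan on day 84: 0.531 − 0.078 = 0.453; × 0.3 = 0.136; × 0.5 = 0.227.

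*New lesions keep arising after growth, at constant hazard (1 − g)λ, with λ = ln 2/91 = 0.00762 per day.* Missed share = S(scan) × exp[−λ(1 − g)(335 − scan)] − S(335).
- Scan on day 56, g = 0.3: 0.658 × exp(−0.00762 × 0.7 × 280) − 0.078 = 0.148 − 0.078 = 0.070.
- Scan on day 56, g = 0.5: 0.226 − 0.078 = 0.148.
- Scan on day 84: 0.139 − 0.078 = 0.061 and 0.204 − 0.078 = 0.126.

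*Effect on the median.* Use the second model with the scan on day 56, and date each event at the assessment that finds it (56, 168, 252 or 336; day numbers used as elapsed days). The recorded median is the first assessment with at least 50% progressed:

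| True median (days) | Growth also assessed | As listed, g = 0.3 | As listed, g = 0.5 |
|---|---|---|---|
| 45 | 56 | 56 | 56 |
| 60 | 168 | 168 | 168 |
| 90 | 168 | 168 | 168 |
| 120 | 168 | 168 | 252 |
| 180 | 252 | 252 | 336 |

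The median moves only when progression is slow and growth makes up a large share.

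**The case against.** The strongest reply is that this is a journal article. The definition of progression, its date and its source usually stand in the full protocol, the case report form or the analysis plan, none of which is shown. Footnote 15 also covers survival, ECOG and new antitumour treatment, and a decline in ECOG or a change of treatment often signals progression. Unscheduled visits are possible.

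Much of this stands. A reader might infer that visits 16 to 18 record nothing but new lesions, that growth of known lesions never counts, and that time to progression is therefore overstated. The article does not support those readings:
- three other kinds of information are recorded;
- growth seen at the visit 15 scan can count;
- progression is undefined for this endpoint, and no follow-up form is shown;
- footnote 15 belongs to the group 1 table. The corresponding row for group 2 in Table 3 has no footnote, and those patients have their tumours resected.

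The percentages rest on an assumed median and an assumed growth share. They ignore deaths, although entry requires an anticipated life expectancy of only 6 months or more.

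The reply does not remove the point. The article presents Tables 2 and 3 as the complete schedules, and it names the tumour item at follow-up and confines it to new lesions. A change of treatment or ECOG may hint at progression but neither establishes it nor dates it.

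**Conclusion.** The point holds for group 1 in this form: after the single scan between day 49 and day 84, no scheduled imaging and no listed item captures growth of known lesions, although the endpoint runs to 1 year. If progression includes such growth, time to progression is likely biased upwards, and this gap cannot bias it downwards. The amount is unknown.

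Under the assumptions above, about 7-15% of patients would be missed by day 336 with a day-56 scan (6-13% with a day-84 scan) if new lesions continue to arise after growth. The upper bounds are 17-29% and 14-23%. If most patients progress by the scan, the median does not change.

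Time to progression is a lower-ranked secondary endpoint in a trial of 6 + 16 patients whose primary endpoint is safety, and no stated decision depends on it. That makes this a minor-to-moderate point.

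**What to change.** At visits 16 to 18, add three items to disease status: first progression of any kind (growth of known lesions, new lesion or clinical), its date, and its basis, taken from routine scans already done since the last contact. Analyse the recorded date, not the visit date. Where an event is known only to lie between two assessments, treat it as interval-censored; between the scan and visit 16 that interval is 70 to 133 days. State in the analysis plan that progression includes growth of known lesions.

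If these data cannot be collected, limit the endpoint to progression status at the day-56 scan.

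The cost is three data fields and a short passage in the analysis plan, with no added scans. The downside is that routine scans are not uniformly timed, so dates after visit 15 will be less regular than those from a scheduled scan.
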